## Temporary Halt

A temporary halt of a study is defined as an unforeseen interruption not provided in the protocol but with the intention to resume it. If the reason for the temporary halt may have a negative effect on benefit-risk assessment, re-start is possible only after approval of a substantial modification.

## Early Termination of the Study

Early termination is defined as the premature end of a clinical study before at least the last patient has completed visit 3 .

The following reasons or events may result in an early termination:

- New findings on the study intervention lead to doubt as to the benefit-risk ratio;
- Subject enrollment is insufficient;
- DSMB recommends termination of the entire study or single treatment arms.

An early end of the study due to early inclusion of the total number of subjects is not considered an early termination. In the event of premature discontinuation of the study for any reason whatsoever, the regulatory authorities should be informed according to applicable regulatory requirements. In case of an early termination of the study, the date of early termination will be the date of end of study.

## Premature Closure of a Site

Premature closure of a single site by coordinating investigator may be considered for the following reasons:

• Study centers that fail to recruit any subject in the first 6 month after initiation.

• Study centers that fail to meet the minimum recruitment goal of 3 subjects within 12 months.

• Non-compliance with ICH-GCP, any provision of the study protocol or breach of the applicable laws and regulations of the investigator, sub-investigator or delegated staff.

The investigator may terminate participation in the study himself/herself if at his/her own discretion the site or the investigator becomes unable to perform or complete the study according to the agreement in place.

# Adverse Events

## Definitions

- - 1. Adverse Event

Following GCP, the definition of an adverse event (AE) is adapted as follows: Any untoward medical occurrence in a subject participating in a study and which does not necessarily have a causal relatedness with the study intervention. An AE can therefore be any unfavorable and unintended sign, symptom, or disease temporally associated with the study intervention, whether or not related to the study intervention.

An AE may be:

- New symptoms / medical conditions,
- New diagnosis,
- Intercurrent diseases and accidents,
- Worsening of medical conditions/ diseases existing before study start,
- Recurrence of disease,
- Increase of frequency or intensity of episodic diseases.

A pre-existing disease or symptom will not be considered an adverse event unless there will be an untoward change in its intensity, frequency or quality. This change will be documented by an investigator.

Surgical procedures themselves are not AEs; they are therapeutic measures for conditions that require surgery. The condition for which the surgery is required may be an AE. Planned surgical measures permitted by the study protocol and the condition(s) leading to these measures are not AEs, if the condition leading to the measure was present prior to inclusion into the study. In the latter case the condition should be reported as medical history.

AEs are classified as "non-serious" or "serious".

- - 1. Serious Adverse Event

Serious adverse event (SAE) is untoward medical occurrence that:

- Results in death,
- Is life-threatening (the term life-threatening refers to an event in which the subject was at risk of death at the time of event and not to an event which hypothetically might have caused death if it was more severe),
- Requires hospitalization or prolongation of existing hospitalization,
- Results in persistent or significant disability / incapacity*,
- Is a congenital anomaly / birth defect,
- Is otherwise medically relevant.

* Persistent or significant disability or incapacity means that there is a substantial disruption of a person's ability to carry out normal life functions. The irreversible injury of an organ function (e.g. paresis, diabetes, cardiac arrhythmia) fulfils this criterion.

Medical and scientific judgement should be exercised in deciding whether expedited reporting to coordinating investigator is appropriate in other situations - such as important medical events that may not be immediately life threatening or result in death or hospitalization but may jeopardize the subject or may require intervention to prevent one of the other outcomes listed above. These should also usually be considered serious (examples of such events are intensive treatment in an emergency room or at home for allergic bronchospasm; blood dyscrasias or convulsions that do not result in hospitalization).

However, since the following events do not change the ongoing benefit-risk assessment of the present study, they do not need to be reported as SAEs:

- Hospitalization aiming exclusively at diagnostic measures or due to technical, practical or social reasons, i.e. hospitalization without underlying adverse event

## Characteristics of Adverse Events

- - 1. Grading of AEs

The grading of AEs in this study will be carried out on the basis of the 5-grade scale defined in the CTCAE V 5.0:

| Grade 1: | Mild; asymptomatic or mild symptoms; clinical or diagnostic observations only; intervention not indicated. |
| --- | --- |
| Grade 2: | Moderate; minimal, local or non-invasive intervention indicated; limiting age-appropriate instrumental Activities of Daily Living (ADL)*. |
| Grade 3: | Severe or medically significant but not immediately life-threatening; hospitalization or prolongation of hospitalization indicated; disabling; limiting self-care ADL**. |
| Grade 4: | Life threatening consequences; urgent intervention indicated. |
| Grade 5: | Death related to AE. |

*Instrumental ADL refer to preparing meals, shopping for groceries or clothes, using the telephone, managing money, etc.

**Self-care ADL refer to bathing, dressing and undressing, feeding self, using the toilet, taking medications, and not bedridden.

The grading of all AEs listed in the CTCAE v 5.0 will be based on the information contained therein. The grading of all other AEs, i.e., those which are not listed in the CTCAE v 5.0 will be performed by a responsible investigator, based on definitions given above.

If an AE shows an undulating course of intensity, it must be documented only once with predominant or medically most appropriate intensity / with the highest intensity grade.

- - 1. Causal Relatedness

The investigator will evaluate each AE that occurred after randomization regarding the **relatedness** with the study intervention:

| Related | There is a reasonable possibility of a causal relatedness between the event and the study intervention, i.e. the possibility for a causal relatedness between the study intervention and the AE cannot be excluded. |
| --- | --- |
| Not related | There is no reasonable possibility of a causal relatedness between the AE and the study intervention, i.e. there is a clear alternative explanation. |

- - 1. Outcome of AEs

All subjects who have reportable AEs, whether considered associated with the use of the study intervention or not, must be monitored to determine the outcome. The clinical course of the AE will be followed up until resolution or normalization of changed laboratory parameters or until it has changed to a stable condition. This also holds for ongoing AEs/SAEs of withdrawn subjects.

The **outcome** of an AE at the time of the last observation will be classified as:

| Recovered / resolved: | All signs and symptoms of an AE disappeared without any sequels at the time of the last interrogation. |
| --- | --- |
| Recovering / resolving: | The intensity of signs and symptoms has been diminishing and / or their clinical pattern has been changing up to the time of the last interrogation in a way typical for its resolution. |
| Not recovered / not resolved: | Signs and symptoms of an AE are mostly unchanged or worsened at the time of the last interrogation. |
| Recovered / resolved with sequelae: | Actual signs and symptoms of an AE disappeared but there are sequels related to the AE. |
| Fatal: | Resulting in death. If there are more than one adverse event only the adverse event leading to death (related) will be characterized as ‘fatal‘. |
| Unknown | The outcome is unknown or implausible and the information cannot be supplemented or verified. |

- - 1. Countermeasures

The term “countermeasures” refers to the specific actions taken to treat or alleviate adverse events or to avoid their sequels. Following categories will be used to categorize the countermeasures to adverse events:

| None: | No action taken. |
| --- | --- |
| Drug treatment: | Newly-prescribed medication or change in dose of a medication. |
| Others: | Other countermeasures, e.g. an operative procedure. |

##

## Period of Observation and Documentation

Adverse events (AEs) will be ascertained by the investigators using non-leading questions, noted as spontaneously reported by the subjects to the medical staff at any time during the study or observed at any of the study visit.

The observation period begins with randomization and ends with the last study visit.

AEs with a grading ≥ 2 will be documented in the subject file and in the CRF. AEs of grade 1 will not be documented in the subject file and in the CRF. If applicable, all medical diagnoses or symptoms occurring prior to the beginning of the period of observation and documentation will be recorded in the CRF as medical history.

The following general rules apply to the documentation of the AEs and SAEs: The start date of an SAE must not be earlier than that of the corresponding AE. The end date of a SAE is typically the same as that of AE. The end date of the SAE must not be later than the end date of the corresponding AE. AEs and SAEs that are ongoing at the time of death are considered not resolved or resolving.

All SAEs and their relevance for the benefit-risk assessment of the study will be evaluated continuously during the study and for the final report. All SAEs will be documented in the CRF.

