## Secondary Objectives and Endpoints

The secondary objectives are to compare side effect profile and safety as well as psychopathological changes between mECT plus TAU versus TAU only.

The secondary endpoint for treatment efficacy is the proportion of relapse free subjects at the end of phase II.

Further secondary endpoints are:

- BPRS
- Global assessment of functioning (GAF) allowing a general (34) and PANSS allowing a differentiated view on specific symptom dimensions (35)
- HAMD (36) monitoring depression, since ECT and mECT have a well-known positive influence on mood
- The Northoff catatonia rating scale (NCRS-dv) (37) assessing the full spectrum of catatonic symptoms
- Q-LES-Q-18, an abbreviated and validated Quality of Life Enjoyment and Satisfaction Questionnaire for subjects with schizophrenia (38)
- The Self-Stigma of Mental Illness Scale – Short Form (SSMIS-SF) (39) and the Stigma-Stress-Skala (40) are used for self-labeling and stigma
- MMSE (41) and THINC-it (28-30) monitoring cognition

All secondary endpoints listed above are analyzed at the end of phase II and at the end of follow-up.

Safety will be also determined by the frequency of adverse events from randomization up to the last follow-up visit.

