**Visit 3**

Study participation can regularly end at study visit 3.

If the study participation ends prematurely (before visit 3), see section 7.3, the assessments according to visit 3 should be done.

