## Permanent Discontinuation from Study Intervention / Study

Permanent discontinuation from study intervention is any discontinuation associated with the investigator’s or the subject’s definitive decision not to re-initiate the study intervention. The following criteria will lead to a permanent discontinuation from study intervention:

- Subject’s request, i.e. withdrawal of consent,
- Loss to follow up,
- Relapse (BPRS > 120% of baseline [visit 2]) during a study visit or during an unplanned visit
- Unplanned hospitalization due to worsening psychiatric symptoms.
- The treatment is postponed more than once for at most one week or the treatment is postponed more than one week.

All subjects who discontinue the study prematurely, a withdrawal examination at least with respect to the secondary endpoint is offered at any time up to week 28 of the subject study inclusion (time of randomization, Visit 2). The subject must be asked to consent to this last examination. The (oral) consent must be documented in the patient file. The withdrawal examination must be documented in the CRF.

For details concerning sample and statistical considerations see chapter 9.

- - 1. Lost to Follow-Up

Subjects will be considered lost to follow-up if they fail to show up for study visits and cannot be contacted by the site. Site personnel is expected to make diligent attempts to contact subjects who did not show up for a scheduled visit or were otherwise not available. These contact attempts should be documented in the subject’s medical record.

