## Secondary Analyses

The number of relapse free subjects at the end of phase II will be analyzed by a mixed logistic regression model (two-sided alpha=0.05) with planned treatment, strata and BPRS at baseline as fixed effects and site as random effect in all subjects randomized (ITT).

BPRS, GAF, PANSS, HAMD, NCRS-dv, Q-LES-Q-18, SSMIS-SF and stigma-stress-scale will be categorized considering relapses and dropouts as additional categories. These will be tabulated using standard descriptive measures including number of non-missing values, mean, standard deviation, extrema and quartiles.

Furthermore, to analyze BPRS, GAF, PANSS, HAMD, NCRS-dv, Q-LES-Q-18, SSMIS-SF and stigma-stress-scale per time-point linear mixed models with the respective scale at baseline, strata and treatment as fixed effects and site as random effect will be used.

An explorative analysis will be carried out for all recruited subjects, where a logistic regression will be performed for the rate of inclusion in the randomized trial on baseline criteria. This way, subjects likely to profit from a first session of ECT can be determined based on clinical criteria.

**Safety analysis:** Frequencies of subjects experiencing at least one adverse event (AE) will be displayed according to MedDRA terminology. MMSE and THINC-it will be analyzed by group using standard descriptive measures.

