## Sample Size / Power Calculation

Relapse rates after 6 months of treatment in phase II are estimated to be 90% in the TAU arm and 40% in the mECT + TAU arm based on a clinical trial with a similar study design, a systematic review and a recent open label CRS mECT study (24, 25, 42). In this calculation, more conservative relapse rates of 85% (TAU) and 45% (mECT + TAU) are assumed; although most evidence indicates even lower relapse rates for mECT + TAU, but our subjects might be more severely affected drug resistant subjects. We are aiming for sufficient power for the composite endpoint strategy where missing values are treated as relapses, which increases the relapse rates. With expected rates of missing values of 15% (TAU) and 30% (mECT + TAU) due to higher inconvenience with mECT +TAU, the relapse rates for planning the sample size are 87.25% (TAU) and 61.5% (mECT + TAU). This yields hazard rates of 0.3433 and 0.1591 and a hazard ratio of 0.4634, which in this case is a conservative approach.

Including 84 subjects (42 per group) in phase II, a difference could be found with a power of 0.85 using a cox regression with alpha= 0.05 (two-sided) and considering the reduced effect due to missing values as specified above. Even if the expected hazard rate in the MECT+TAU arm is 0.17 (≙ 63.9%) e.g. due to lower effects or due to a bias because of different observation schedules, the power is still ~80%. (The necessary sample size was simulated using R.) 140 subjects must be enrolled in phase I, if 60% of subjects are responders and willing to participate in phase II of the trial.

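### The only AE measure fixed is a crude count of subjects over a window of unequal length, so equal AE rates would give unequal percentages, in a direction the protocol leaves open

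*Protocol*

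**What the plan says.** Comparing side effects and safety between the arms is listed first among the main secondary objectives in the Synopsis and appears again in section 2.2.

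- **Window.** Section 8.3: "The observation period begins with randomization and ends with the last study visit". Section 2.2 words the end point differently: "Safety will be also determined by the frequency of adverse events from randomization up to the last follow-up visit".
- **Measure.** Section 9.5: "Frequencies of subjects experiencing at least one adverse event (AE) will be displayed according to MedDRA terminology". No person-time denominator, time-to-event method or common cut-off is named.
- **End of participation.** Section 6, Visit 3: "Study participation can regularly end at study visit 3". The same paragraph asks for the visit 3 assessments if a subject leaves sooner. Section 7.2 says of early leavers that "a withdrawal examination at least with respect to the secondary endpoint is offered at any time up to week 28". Others continue to visit 4b, 12 months after visit 3. In that period patients choose whether to have mECT, whichever arm they were assigned to (section 6, Follow-Up period).
- **Expected exits.** Section 9.9: "more conservative relapse rates of 85% (TAU) and 45% (mECT + TAU) are assumed", and "With expected rates of missing values of 15% (TAU) and 30% (mECT + TAU) due to higher inconvenience with mECT +TAU". Combined, these give planning rates of 87.25% (TAU) and 61.5% (mECT + TAU).
- **Relapse.** Section 7.2 lists relapse and unplanned psychiatric admission as reasons to stop the study intervention for good. The section title covers both intervention and study, and the text does not say whether these subjects keep attending visits.

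**The concern.** A count of subjects with one or more AEs rises with time observed. If one arm is watched longer, it shows a higher percentage even when the monthly AE rate is the same in both. Here the plan expects the arms to lose subjects at different rates, so unequal observation is foreseeable. Counting through follow-up adds a second problem: AEs under self-chosen treatment are attributed to the randomized arm. At stake is a between-arm safety comparison that the count alone cannot deliver.

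**Working it through.** **Inputs (section 9.9).** Relapse 85% / 45%, missing 15% / 30%, 42 per arm, six-month horizon. Exponential exit times and the AE rate *r* are my assumptions.

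**Step 1: reproduce the plan's figures.**

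- Composite rate = relapse × (1 − missing) + missing. TAU: 0.85 × 0.85 + 0.15 = 0.8725. mECT + TAU: 0.45 × 0.70 + 0.30 = 0.615.
- Monthly hazard *h* = −ln(1 − rate)/6. TAU: −ln(0.1275)/6 = 0.3433. mECT + TAU: −ln(0.385)/6 = 0.1591.
- Hazard ratio = 0.1591/0.3433 = 0.4634. All agree with section 9.9.

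**Step 2: dropout alone.** −ln(0.85)/6 = 0.0271 (TAU) and −ln(0.70)/6 = 0.0594 (mECT + TAU).

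**Step 3: mean observed time in months.** Phase II: (1 − e^(−6h))/h. With follow-up, add 12 × e^(−6h), which supposes that everyone reaching visit 3 stays the full 12 months.

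| What ends AE observation | TAU | mECT + TAU | Ratio mECT/TAU |
| --- | --- | --- | --- |
| A. Relapse or dropout, phase II | 0.8725/0.3433 = 2.54 | 0.615/0.1591 = 3.87 | 1.52 |
| B. As A, plus follow-up | 2.54 + 12 × 0.1275 = 4.07 | 3.87 + 12 × 0.385 = 8.49 | 2.08 |
| C. Dropout only, phase II | 0.15/0.0271 = 5.54 | 0.30/0.0594 = 5.05 | 0.91 |
| D. As C, plus follow-up | 5.54 + 12 × 0.85 = 15.7 | 5.05 + 12 × 0.70 = 13.4 | 0.85 |

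Taking 28 weeks instead of six months gives 1.55, 2.13, 0.91 and 0.85.

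**Step 4: percentage of subjects with an AE at the same rate *r* in both arms.** Phase II: r/(r + h) × (1 − e^(−6(r+h))). With follow-up: 1 − [h/(r + h) × (1 − e^(−6(r+h))) + e^(−6h) × e^(−18r)].

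For example, A with r = 0.1:

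- TAU: 0.1/0.4433 × (1 − e^(−2.66)) = 21%.
- mECT + TAU: 0.1/0.2591 × (1 − e^(−1.555)) = 30%.

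| mECT + TAU vs TAU | r = 0.05 | r = 0.1 | r = 0.2 |
| --- | --- | --- | --- |
| A | 17% vs 12% | 30% vs 21% | 49% vs 35% |
| B | 30% vs 16% | 45% vs 26% | 60% vs 39% |
| C | 22% vs 24% | 39% vs 42% | 61% vs 66% |
| D | 45% vs 52% | 65% vs 75% | 80% vs 89% |

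Per arm of 42, the phase II gap at r = 0.1 is about four subjects in A (42 × 0.304 = 12.8 vs 42 × 0.210 = 8.8). In C it is one or two the other way (16.2 vs 17.6).

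**Step 5: scope.** Section 8.1.1 counts worsening and recurrence of disease as AEs, so a relapse of grade 2 or more is itself a documented AE. Observed relapses on the plan's rates would be about 0.85 × 0.85 = 72% (TAU) and 0.45 × 0.70 = 32% (mECT + TAU). The percentages in step 4 therefore describe non-relapse AEs only.

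**The case against.** The strongest reply is that section 9.5 describes a descriptive display with no test, that section 9.3 leaves detail to the SAP, and that the SAP could add exposure-adjusted rates. That is true, and the absence of such a table from a protocol would not by itself be a finding. But the protocol itself fixes the crude count, a window running into self-chosen treatment, and an unclear status for relapsed subjects. When AE collection stops is also a matter of conduct, to be settled while data are being collected.

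Three stronger readings are tempting and are not supported:

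- **That the imbalance is at most 1.5-fold and follows directly from the plan's rates.** It holds only if relapse ends AE observation and only phase II is counted. Section 7.2 ties relapse to stopping the intervention, and section 2.2 counts AEs to the last follow-up visit. Across the four cases the ratio runs from 0.85 to about 2.1.
- **That no AE query is required when a subject leaves.** Section 6.2 has AEs asked for at each contact, section 6 asks for visit 3 assessments at early exit, and the Schedule of Assessment marks AEs at visit 3 and at unscheduled visits. What remains is a mismatch: section 7.2 only offers an exit examination with narrower minimum content, and section 6 refers for premature end to section 7.3, which deals with a temporary halt.
- **That the better mECT prevents relapse, the more harmful it must look.** Relapses count as AEs, so the overall count could well favour mECT. Even for other AEs, the direction depends on whether relapse ends observation.

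One objection to the remedy also stands. mECT sessions thin out from weekly to every three weeks (section 5.1), so a person-month rate, which assumes a roughly constant risk, is not neutral.

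**Conclusion.** The point holds in this limited form. The protocol's one AE measure ignores time at risk, while its own planning rates imply unequal time at risk in all four cases examined. In phase II the ratio of mean observed time is 0.91 or 1.52, depending on whether relapse ends AE observation; with follow-up it is 0.85 or about 2.1. Neither the size nor the direction of the distortion can be fixed from the document. The ratios rest on the plan's rates and an exponential model. The percentages also rest on an assumed equal non-relapse AE rate. The primary analysis is not affected. This should be corrected because safety is a stated comparison and the remedy is cheap.

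**What to change.** 1. **Section 9.5.** Keep the crude count as description. Add AE and SAE incidence for phase II by randomized arm that accounts for time at risk: first event per person-month, or cumulative incidence with exit accounted for. Show observed time by arm beside it. List relapse and psychiatric-worsening events apart from other AEs, and report follow-up AEs separately.
2. **Sections 2.2, 6 (Visit 3), 7.2 and 8.3.** Reconcile them on whether relapsed subjects remain under AE observation and when it ends.
3. **Sections 6 (Visit 3) and 7.2.** Reconcile the content of the exit examination, and correct the cross-reference to section 7.3.
4. **Data.** Make the date on which AE observation ended available for each subject. Withdrawal dates and AE start and end dates are already collected, so at most one field is needed.

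The cost is one or two extra tables and no extra visits. Because the person-month rate assumes a roughly constant risk, cumulative incidence may be shown with it.
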